### Sample Size

Reginster and colleagues [53] conducted an RCT of glucosamine vs. placebo in patients with OA, and reported no loss in joint space width (mean -0.06 mm) in the glucosamine group vs. a -0.31 mm joint space loss in the placebo group (p = 0.043). Radiographic joint space loss has been shown to be closely related to reduction in cartilage thickness by MRI, our primary outcome [54]. We conservatively assumed, given the lack of published data, that the protective effect of PRT would be 20% less than that of glucosamine (i.e. 80% rather than 100% reduction in cartilage loss). Therefore, our sample size was estimated from the expected rate of cartilage thinning in sedentary patients with OA of -2.8 ± 2.7% per 6 months [55], which we hypothesized would be unchanged by sham exercise in the controls but would be reduced by 80% to -0.56 ± 2.7% by PRT exercise. The sample size was inflated by 20% to accommodate the anticipated dropout rate over 6 months, based on previous exercise and OA trials in the literature and in our experience. Therefore, the final sample size targeted was 63.

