### Covariates

Covariates identified *a priori *included age, BMI, duration of OA, use of glucosamine and/or chondroitin sulfate, number of chronic diseases. Other covariates will be selected if potential confounders are identified amongst baseline participant characteristics.

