### Randomization

Using a computerized randomization program , a co-investigator uninvolved in participants testing or training randomly allocated participants into 1 of 2 groups. Participants were stratified according to glucosamine and/or chondroitin use (current or within the past 6 months) and Physical Function (Section C; Disability) WOMAC score (< or > 27) in order to equalize these potential confounders between groups. After completion of baseline assessments, participants were given a sealed envelope containing the allocated group (A or B) in accordance with the randomization sequence.

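### The 2.24-point planned difference makes no allowance for the glucosamine users enrolled, and is too large unless the cohort behind the -2.8% had a similar share of users

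*Protocol article*

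**What the plan says.** All references are to the protocol article.

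- **Sample Size, sham arm.** The planning value is an "expected rate of cartilage thinning in sedentary patients with OA of -2.8 ± 2.7% per 6 months", "which we hypothesized would be unchanged by sham exercise in the controls".
- **Sample Size, PRT arm.** The loss "would be reduced by 80% to -0.56 ± 2.7% by PRT exercise".
- **Sample Size, origin of the 80%.** A randomised trial of glucosamine against placebo "reported no loss in joint space width (mean -0.06 mm) in the glucosamine group", against -0.31 mm on placebo. The section carries this over to the trial's own endpoint: "Radiographic joint space loss has been shown to be closely related to reduction in cartilage thickness by MRI, our primary outcome". It then assumes that "the protective effect of PRT would be 20% less than that of glucosamine (i.e. 80% rather than 100% reduction in cartilage loss".
- **Eligibility Criteria.** Use of glucosamine or chondroitin is not among the exclusions.
- **Randomization.** "Participants were stratified according to glucosamine and/or chondroitin use (current or within the past 6 months"; the stated purpose is to balance a potential confounder.
- **Covariates.** The a priori list contains "use of glucosamine and/or chondroitin sulfate".
- **Statistical analysis.** The ANCOVA of percentage change adjusts for baseline value. Further covariates are considered if they differ between the groups at baseline and are related to the outcome. No group-by-stratum term is named.

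The article gives no expected share of users. It does not say whether the cohort behind the -2.8% used glucosamine.

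**The concern.** The Sample Size section relies on glucosamine nearly abolishing cartilage loss when it chooses the PRT effect, and leaves that premise aside when it sets the sham loss. On the premise, women already taking glucosamine have little loss left to prevent, so a sham arm that includes them should lose less than a sham arm of non-users. Stratification spreads users evenly over the arms, and covariate adjustment removes outcome variance. Neither restores a mean difference that is smaller because part of the cohort has less to lose.

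At stake is how a null result would be read. If the pooled difference falls short because the planned contrast applied to only part of the cohort, the trial could be reported as showing that PRT does not modify disease, with no prespecified analysis to show otherwise.

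**Working it through.** **Inputs from the article.** Sham loss 2.8%, SD 2.7%, PRT reduction 80%, dropout 20%, target 63, significance level 0.05, glucosamine result -0.06 mm against -0.31 mm.

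**Inputs assumed here.** 1:1 allocation, two-sided test, two-sample t-test, user share *g* of 10% to 50%, -2.8% applying to non-users, PRT removing 80% of whatever loss remains, and SD 2.7 within each stratum.

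**Step 1: the plan's own figures.**
- PRT loss: 2.8 x (1 - 0.80) = 0.56.
- Difference: 2.8 - 0.56 = 2.24 points; standardised, 2.24 / 2.7 = 0.83.
- Target: one-sided 0.05 with 90% power (normal approximation) gives 25 per arm, and 50 / 0.8 = 62.5, so 63. Two-sided 0.05 with 80% power gives 46 in total, and 46 / 0.8 = 57.5, so 58. The 63 can be matched, but only with choices the article does not state.
- Completers: 63 x 0.8 = 50.4, about 25 per arm.

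**Step 2: difference in a mixed cohort.** If users lose *u*, the difference is 0.8 x [2.8(1 - g) + u g].
- If users lose nothing (the 100% reduction the plan uses), u = 0 and the difference is 2.24(1 - g).
- If users keep the share of loss in the cited figures, u = 2.8 x 0.06 / 0.31 = 0.54.

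Power is for 25 per arm in the pooled comparison. The last column is the comparison in non-users alone, with 25(1 - g) per arm and a difference of 2.24.

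| User share | Difference, u = 0 | Power | Difference, u = 0.54 | Power | Power, non-users only |
|---|---|---|---|---|---|
| 0% | 2.24 | 82% | 2.24 | 82% | 82% |
| 10% | 2.02 | 73% | 2.06 | 75% | 78% |
| 20% | 1.79 | 63% | 1.88 | 67% | 72% |
| 30% | 1.57 | 52% | 1.70 | 59% | 66% |
| 50% | 1.12 | 30% | 1.34 | 40% | 51% |

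On these assumptions the non-user comparison has more power than the pooled one, although it uses fewer women.

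**Step 3: leaving the stratum out of the model.** With u = 0, users and non-users differ by 2.8 points in the sham arm and 0.56 in the PRT arm. The unadjusted variances are then 2.7² + g(1 - g) x 2.8² and 2.7² + g(1 - g) x 0.56². Averaging them, power at 30% users falls from 52% to 48%. A stratum term absorbs the average gap, (2.8 + 0.56) / 2 = 1.68, and leaves 1.12 in each arm. Since 1.12² = 1.25 and the average of 2.8² and 0.56² is 4.08, it removes about 69% of the extra variance.

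**Step 4: dependence on the source cohort.** Suppose that cohort had a user share *s*, with users losing nothing. The non-user loss is then 2.8 / (1 - s), and the difference in this trial is 2.24(1 - g) / (1 - s). If s = g, it is 2.24 and nothing is lost. If s = 10% and g = 20%, it is 2.24 x 0.8 / 0.9 = 1.99. If s exceeds g, 2.24 is too small rather than too large.

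**The case against.** A reader might infer that the 2.8% was planned for untreated women and that 2.24 points is therefore shown to be wrong. The article does not support this. It describes the source cohort as sedentary and says nothing of its glucosamine use. If it was an ordinary osteoarthritis cohort with a similar share of users, the -2.8% is already a mixed-population mean. This objection stands and is why the point is conditional.

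Other points also stand:

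- Stratifying on use shows that users could enter. It does not show that there were many. The range of shares is an assumption.
- The stratum includes chondroitin-only users and women who stopped within the past 6 months. The cited result is for glucosamine, and it concerns joint space width, which reaches cartilage thickness only through the link the article asserts. Assigning zero or 0.54% loss to the whole stratum goes further than the article does.
- The rationale for resistance training gives a second pathway, in which loading may stimulate cartilage synthesis. The assumption that PRT acts only on remaining loss sets that pathway aside, so it cannot be said that the plan rules out benefit in users.
- The 82% reference power is not a claim of the plan.
- A condensed article may leave a description of the source cohort to the full protocol.

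The objection does not remove the inconsistency within Sample Size: glucosamine's effect sets the PRT effect but plays no part in the sham loss. Nor does listing glucosamine use as an a priori covariate settle the model. The Statistical analysis section does not say the factor is always included, and the only entry route it describes depends on a baseline difference, which stratification makes unlikely.

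**Conclusion.** The concern holds conditionally. Unless the cohort behind the -2.8% had a similar share of glucosamine/chondroitin users, 2.24 points is too large for the population enrolled. If users lose nothing, the difference is 2.02, 1.79 or 1.57 points at 10%, 20% or 30% users, and power falls from 82% to 73%, 63% or 52%. The loss is smaller if users keep some cartilage loss, if the source cohort included some users, or if PRT also builds cartilage in users. These figures rest on the assumptions listed in the check, including a power basis the article does not state. Neither the difference of 2.24 nor the target of 63 is shown to be an error.

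**What to change.** 1. In Sample Size, state that 2.24 points applies to women losing cartilage at -2.8% per 6 months and would be smaller in a cohort that includes users, unless the source cohort had a similar share. If the source cohort's glucosamine use is known, report it.
2. In Statistical analysis, include the glucosamine/chondroitin randomisation stratum in the primary ANCOVA regardless of observed imbalance.
3. Prespecify, as a supporting analysis, the PRT-sham difference in non-users with its confidence interval, estimated from the same ANCOVA with a group x stratum term.

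Reworking the target with the recorded user share would add little, since recruitment ended in December 2006.

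**Cost.** Some wording and a model term, with no new data. The non-user estimate rests on fewer women (about 17 or 18 per arm at 30% users), and the interaction test has low power. The analysis must be reported as supporting, not as a replacement for the pooled primary comparison. The stated detectable difference also becomes less favourable.

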### Randomization

Using a computerized randomization program , a co-investigator uninvolved in participants testing or training randomly allocated participants into 1 of 2 groups. Participants were stratified according to glucosamine and/or chondroitin use (current or within the past 6 months) and Physical Function (Section C; Disability) WOMAC score (< or > 27) in order to equalize these potential confounders between groups. After completion of baseline assessments, participants were given a sealed envelope containing the allocated group (A or B) in accordance with the randomization sequence.

### Statistical analysis

Data were inspected for normality visually and statistically (skewness -1 ≥ 1), and expressed as mean and standard deviation or median and range, as appropriate. Non-normally distributed data were log-transformed prior to use with parametric statistics if possible or used with non-parametric tests if assumptions of normality were not met despite transformation. Our primary analytic strategy was a complete case analysis because of the novelty of our primary outcome. Our secondary sensitivity analysis was intention-to-treat with data imputed via the expectation maximization algorithm (covariates included in the model were group, baseline score, and compliance). Comparisons between groups were made using repeated measures analysis of co-variance (ANCOVA) for both time and group × time interactions, and ANCOVA models for % change scores adjusted for baseline value of each outcome for normally distributed continuous data. Additional covariates considered for inclusion in these models were characteristics at baseline which were different between groups and related to the dependent variable of interest. The Kruskal-Wallace test or Mann-Whitney U test were used for non-normally distributed continuous data. SPSS (Release 13.0 for Windows, 2004, Chicago: SPSS Inc) was used for all data analysis. All *P *values of less than 0.05 were considered statistically significant except for post-hoc comparisons of pairs of variables from significant Kruskal-Wallace models, which were adjusted for multiple comparisons using the method of Bonferroni. Clinical meaningfulness of differences observed was assessed by evaluation of the magnitude of the differences relative to clinical outcomes in the literature, and calculations of effect sizes (Formula 1) adjusted via Hedges bias-corrected effect size for small sample sizes [56]. Effect sizes were interpreted according to Cohen's interpretation of 'trivial' ( < 0.20), 'small' (≥ 0.20 < 0.50), 'moderate' (≥ 0.50 < 0.80), and 'large' (≥ 0.80) effect size [56]. Caution was taken when using Cohen's interpretations as these were originally based on psychological studies. 95% confidence intervals (CIs) for the relative ES were calculated.

$$\begin{array}{cc} \text{Effect Size}=\frac{\Delta \text{ Treatment}-\Delta \text{ Control}}{\text{Pooled SD}} & \left(\text{Formula }1;(56)\right) \end{array}$$

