### Definitions

Session compliance was defined as the number of sessions attended out of 78 available sessions (up to 1 month extension was given to make up any missed sessions during the 6-month intervention). Training intensity compliance was defined as the difference between the theoretical relative load and the actual relative load for exercise for each session. The theoretical relative load (relative to the most recent 1RM) and the actual relative load was calculated at 4, 8, 12, 16, 20, 24, and 26 weeks. The actual load was then subtracted from the theoretical relative load to get difference in relative loads. Difference should be equal to zero if training intensity compliance was perfect or the results will be negative if actual was greater than theoretical. A one sample t-test was then performed to see whether or not the difference in loads was significantly different than "zero", the ideal value.

Total tonnage per exercise was calculated by summating the training load by the number of repetitions completed for that exercise for the intervention (24 repetitions for 78 sessions (total of 1872 repetitions) per exercise for the PRT group and 16 repetitions for 78 sessions (total of 1248 repetitions) per exercise for the sham-exercise group).

Whole body total tonnage was calculated by summating the total summated loads of each exercises and multiplying that by the total number of repetitions of all exercises.

Dropouts were those participants who did not complete the intervention and did not complete their final assessment (i.e. loss to follow-up). Discontinued subjects were those who did not complete the intervention, but did complete their final assessment and were included in the complete case analysis.

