## Discussion and conclusion

Our primary outcome results of cartilage morphology are anticipated in July 2009. This information will provide the first evidence for the efficacy of PRT as a disease-modifying treatment for OA of the knee. Our robustly designed study will be one of very few OA studies that conform to all CONSORT requirements for the reporting of RCTs [57]. In addition, the REACH study will be the first RCT to provide information on the feasibility of using a sham-exercise control group in OA clinical trials.

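### The only intention-to-treat analysis fills missing outcomes by EM with no stated allowance for imputation uncertainty; read as written, its standard errors are too small roughly in proportion to the missing fraction

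*Protocol article*

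**What the plan says.** All of this is in the protocol article.

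- **Primary analysis set** (Statistical analysis): "Our primary analytic strategy was a complete case analysis because of the novelty of our primary outcome".
- **Intention-to-treat analysis** (same section): "Our secondary sensitivity analysis was intention-to-treat with data imputed via the expectation maximization algorithm". For the imputation model, "covariates included in the model were group, baseline score, and compliance".
- **Analysis model** (same section): repeated measures ANCOVA, and "ANCOVA models for % change scores adjusted for baseline value of each outcome". No pooling over several imputed data sets, added residual or corrected variance is described.
- **Who is missing** (Definitions): "Dropouts were those participants who did not complete the intervention and did not complete their final assessment (i.e. loss to follow-up"). Women who stopped the intervention early are a separate group: they "did complete their final assessment and were included in the complete case analysis".
- **How much is expected to be missing** (Sample Size): the target of 63 was "inflated by 20% to accommodate the anticipated dropout rate over 6 months".
- **Visits** (Abstract, Methods): the MRI is done at baseline and 6 months only; the other outcomes are also measured at 3 months.

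**The concern.** The EM algorithm estimates the parameters of a model from incomplete data. When it is used to fill in values, each missing outcome is replaced by its prediction from group, baseline and compliance. Such values carry no residual scatter and add no information about the treatment effect. An ANCOVA run on the completed file does not know this. It divides the residual sum of squares by too many degrees of freedom and counts too many women in the precision of the group contrast.

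The intention-to-treat result is there to show whether the main finding survives dropout. If its interval is too narrow, it can reach significance because of the imputation alone and be read as confirmation. It would do so even when dropout is unrelated to outcome, so it cannot perform its one task.

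**Working it through.** The plan states no figure for the precision of this analysis, so there is none to reproduce. The target of 63 is taken as given and is not in dispute here.

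**Inputs**
- N = 63, anticipated dropout 20%, SD 2.7 percentage points (Sample Size).
- Test level 0.05 (Statistical analysis). Two-sided testing and 1:1 allocation are assumptions; the article states neither.
- Observed at 20% missing: 63 × 0.8 = 50.4, so m = 50 and 13 values are filled.

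**Formula.** Suppose the fill uses group and baseline, and the ANCOVA has the same terms (3 parameters with the intercept). The filled points lie exactly on the fitted surface. The estimated group difference and the residual sum of squares then equal those from the complete cases. Two things change: the residual variance is divided by N − 3 instead of m − 3, and the design counts N women instead of m. Hence

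SE(filled) / SE(complete case) ≈ √[ (m − 3)/(N − 3) × m/N ]

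At 20% missing: √[ 47/60 × 50/63 ] = √(0.7833 × 0.7937) = 0.788, so the standard error is 21% too small.

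**Type I error.** The filled analysis uses the critical value for 60 degrees of freedom, 2.000. On the correct scale this is 2.000 × 0.788 = 1.577. The two-sided tail of t on 47 degrees of freedom beyond 1.577 is 12.2%.

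**Simulation.** 5,000 trials per setting, no true effect, outcomes missing completely at random, outcome correlated 0.3 with baseline, with and without compliance in the fill. Assumed compliance is about 85% in completers and 35% in dropouts. The simulated ratio is mean reported SE over the true SD of the estimate. Paired entries are without / with compliance.

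| Missing | Observed | SE ratio, formula | Type I, formula | SE ratio, simulated | Type I, simulated | Complete-case type I |
|---|---|---|---|---|---|---|
| 5% | 60 | 0.951 | 6.2% | 0.957 / 0.958 | 6.3% / 5.9% | 4.9% / 4.3% |
| 10% | 57 | 0.902 | 7.7% | 0.896 / 0.928 | 7.6% / 7.0% | 5.3% / 4.4% |
| 20% | 50 | 0.788 | 12.2% | 0.766 / 0.790 | 13.3% / 11.7% | 5.4% / 4.9% |
| 30% | 44 | 0.691 | 17.5% | 0.670 / 0.718 | 18.4% / 15.5% | 5.7% / 5.1% |

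At 20% missing, the nominal 95% interval covers the truth 87% of the time without compliance in the fill and 88% with it. The reported standard error is 0.58 to 0.62 points, where complete-case ANCOVA gives 0.73 to 0.74.

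**Variant.** Adding one random residual to each filled value, still in a single data set, leaves type I error at about 10% at 20% missing. Restoring the scatter is therefore not enough; the uncertainty of the imputation model must also be carried through.

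**The case against.** **The article does not say that values are filled once or treated as observed.** That is correct. It is the natural reading of EM-imputed data followed by ANCOVA, but it is an inference. A condensed article may leave the number of imputations to a document that is not shown. If proper multiple imputation was done, the numerical fault disappears and only the wording needs correcting.

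**The 20% is a planning allowance.** This also stands. The understatement follows the dropout that actually occurs and is modest at 5% to 10% missing.

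**It is only a sensitivity analysis.** This stands and limits the severity. The primary inference does not use the filled data, and complete-case ANCOVA held its nominal level in the simulation.

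**A stronger reading is tempting but not supported.** A reader might infer that the complete-case primary analysis abandons the randomised groups and should be replaced. The novelty of an outcome is indeed a thin reason for an analysis set, and dropout could differ between the arms. But under Definitions only women with no final assessment are absent. Women who stopped training but were assessed stay in, and nothing there excludes poor compliers or moves anyone between groups, so this is not a per-protocol set.

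Nor would a replacement mixed model alter the headline. With a single follow-up scan, a baseline-plus-6-month model with a common baseline mean gives essentially the complete-case ANCOVA estimate; in 200 simulated trials with about 20% missing, the largest difference was 6 × 10⁻⁷. The loss of 3-month data concerns secondary outcomes only. Recruitment ended in December 2006 and results were due in July 2009, so changing the declared primary strategy would come after data collection.

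The Discussion's statement that the study will "conform to all CONSORT requirements for the reporting of RCTs" is about reporting and settles nothing on imputation.

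**Conclusion.** The point holds for the intention-to-treat sensitivity analysis and should be fixed. Read as written, its standard errors are about 20% too small and its type I error about 12% at the anticipated 20% dropout. At 5% to 10% missing they are about 4% to 10% too small, with type I error roughly 6% to 7.6%.

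This rests on a single fill treated as observed, two-sided testing at 0.05, roughly equal groups, and outcomes missing completely at random. The last assumption favours the plan: the excess rejections come from the analysis method and not from selective dropout. Selective dropout could add bias, which these figures do not measure.

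**What to change.** Replace the single EM imputation with multiple imputation: at least 20 data sets, the planned ANCOVA in each, and results combined by Rubin's rules. Include group, the two stratification factors (glucosamine or chondroitin use, and WOMAC physical function), baseline score, compliance and, where measured, 3-month outcomes. For secondary outcomes with a 3-month visit, a likelihood-based mixed model using all available visits is an alternative.

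If multiple imputation was already intended, say so and give the number of data sets and the pooling rule. Leave the complete-case primary analysis in place.

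The cost is a change of wording and a little programming, with no new data. Intervals in this sensitivity analysis become wider.

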**Methods:**

Our cohort consisted of women over 40 years of age with primary knee osteoarthritis, according to the American College of Rheumatology clinical criteria. Primary outcome was blinded measurement of cartilage morphology via magnetic resonance imaging scan of the tibiofemoral joint. Secondary outcomes included walking endurance, balance, muscle strength, endurance, power, and velocity, body composition, pain, disability, depressive symptoms, and quality of life.

Participants were randomized into a supervised progressive resistance training or sham-exercise group. The progressive resistance training group trained muscles around the hip and knee at 80% of their peak strength and progressed 3% per session, 3 days per week for 6 months. The sham-exercise group completed all exercises except hip adduction, but without added resistance or progression. Outcomes were repeated at 3 and 6 months, except for the magnetic resonance imaging scan, which was only repeated at 6 months.

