### Primary Outcome: Cartilage Thickness

A 3Tesla MRI scan (Philips Medical Systems, Achieva 3T) of the knee with the most severe clinical signs and symptoms was conducted at the Symbion Clinical Research Imaging Centre at baseline and following the 6-month intervention. OA cartilage morphology assessed via MRI is a reliable and valid technique, particularly for clinical trials where cartilage structure modification is an outcome [35,36]. Depending on the size of the participant's knee, either a SENSE Knee coil (smaller knee) or a SENSE Flex-L coil (larger knee) was used. The same coil was used for pre and post scanning. Prior to the commencement of the scan, a bead was placed on the thigh, halfway between the inguinal groove and the proximal margin of the patella measured anthropometrically by the same observer (AL) in all participants; this marker identified the area for the cross sectional image of the thigh region. The scans included a 3-Dimensional image T1 weighted gradient echo sequence of the tibiofemoral joint (repetition time = 34 ms, echo time = 9 ms, acquisition time = 9 min, flip angle = 25°, slice thickness = 1.4 mm, in-plane resolution = 0.31 mm), and a spin echo sequence of a cross-sectional slice of the thigh region (repetition time = 450 ms, echo time = 10 ms, acquisition time = 2 min, flip angle = 90°, slice thickness = 10 mm, in-plane resolution = 0.47 mm).

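### The EM imputation in the intention-to-treat sensitivity analysis leaves out the observed 3-month score when it fills missing 6-month values of the non-MRI outcomes

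*Protocol article*

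**What the plan says.** The Statistical analysis section sets two layers. The main one is stated as "Our primary analytic strategy was a complete case analysis because of the novelty of our primary outcome". The second reads "Our secondary sensitivity analysis was intention-to-treat with data imputed via the expectation maximization algorithm", and for that imputation "covariates included in the model were group, baseline score, and compliance". No 3-month value is in the list.

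On the schedule, the Methods part of the abstract says "Outcomes were repeated at 3 and 6 months, except for the magnetic resonance imaging scan, which was only repeated at 6 months". The Primary Outcome section agrees for the scan, which "was conducted at the Symbion Clinical Research Imaging Centre at baseline and following the 6-month intervention".

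The Definitions section settles whose 6-month values are missing: "Dropouts were those participants who did not complete the intervention and did not complete their final assessment (i.e. loss to follow-up"). Women who stop training but attend the final visit need no imputation: "Discontinued subjects were those who did not complete the intervention, but did complete their final assessment". It also defines the one post-baseline covariate: "Session compliance was defined as the number of sessions attended out of 78 available sessions".

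**The concern.** Under the stated model, two women in the same arm with the same baseline score and the same attendance receive the same imputed 6-month score, even if one had clearly worsened by month 3 and the other had improved.

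Response-related withdrawal is plausible in this trial. The Intervention section reports pain severe enough to require isometric substitution in some participants, and the Adverse events section describes pain-driven adjustments in both groups. Loading differs sharply between the arms (80% of peak strength against the bare weight of the machine parts), so symptom-driven loss may also differ by arm. That is the situation in which omitting early response distorts the group contrast, in favour of the arm that loses more of its poor responders.

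At stake is the usefulness of the sensitivity analysis for the secondary outcomes, which are part of the stated hypothesis (physical performance, symptoms). Its purpose is to show whether the complete-case result survives dropout, and it should use the information on dropouts that the trial collected.

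**Working it through.** **Inputs from the protocol.** Imputation covariates: group, baseline score, compliance (Statistical analysis). Visits: 3 and 6 months for all outcomes except MRI (abstract). Target sample 63 and anticipated dropout 20% (Sample Size). The protocol gives no figure for the imputation, so there is none to reproduce. It also gives no correlations between visits, no timing of losses and no dropout mechanism; all of these are assumptions below.

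**Step 1: who can be affected.** Expected losses are 0.20 × 63 = 12.6 women. If all leave after the 3-month visit, 12.6/63 = 20% of women with a 3-month value are affected. If half leave before it, 6.3/(63 − 6.3) = 11%. So 20% is a ceiling.

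**Step 2: information left out.** Write r03, r36 and r06 for the correlations baseline–3 months, 3–6 months and baseline–6 months.

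- Variance of the 6-month score explained by baseline: r06².
- Explained by baseline and 3 months: (r06² + r36² − 2·r03·r36·r06)/(1 − r03²).
- Imputation error, in 6-month SDs, for a woman whose 3-month score is one residual SD worse than her baseline predicts: (r36 − r03·r06)/√(1 − r03²).

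For 0.6/0.8/0.6: (0.36 + 0.64 − 0.576)/0.64 = 0.66, and (0.8 − 0.36)/0.8 = 0.55.

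| r03 / r36 / r06 | Baseline only | With 3 months | Error per such woman (SD) |
|---|---|---|---|
| 0.5 / 0.6 / 0.5 | 0.25 | 0.41 | 0.40 |
| 0.6 / 0.7 / 0.5 | 0.25 | 0.50 | 0.50 |
| 0.7 / 0.8 / 0.6 | 0.36 | 0.64 | 0.53 |
| 0.6 / 0.8 / 0.6 | 0.36 | 0.66 | 0.55 |
| 0.7 / 0.85 / 0.65 | 0.42 | 0.73 | 0.55 |

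These are errors for one kind of dropout, not biases in the treatment effect.

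**Step 3: effect on the group contrast.** Simulation with 31 women per arm and 4,000 runs; higher scores are better; true effects are 0.30 SD at 3 months and 0.50 SD at 6 months. The log-odds of dropout are −1.7, less 1.0 for each SD by which the 3-month score exceeds the mean. This dependence is placed in the training arm only, or in both arms. Missing 6-month values are filled with their regression prediction, as a stand-in for EM, and then analysed by ANCOVA on group and baseline. Every simulated dropout has a 3-month value, and attendance is unrelated to response.

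| Correlations | Dependence | No dropout | Listed covariates | Plus 3-month score |
|---|---|---|---|---|
| 0.5 / 0.6 / 0.5 | training arm | 0.496 | 0.550 | 0.495 |
| 0.6 / 0.8 / 0.6 | training arm | 0.500 | 0.565 | 0.499 |
| 0.7 / 0.85 / 0.65 | training arm | 0.497 | 0.556 | 0.497 |
| 0.5 / 0.6 / 0.5 | both arms | 0.504 | 0.489 | 0.501 |
| 0.6 / 0.8 / 0.6 | both arms | 0.499 | 0.486 | 0.500 |
| 0.7 / 0.85 / 0.65 | both arms | 0.500 | 0.485 | 0.499 |

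Dropout was about 16% (training arm only) and 19% (both arms). Bias with the listed covariates is 0.054, 0.065 and 0.059 SD in the first three rows, and −0.015, −0.013 and −0.015 SD in the last three. Adding the 3-month score removes it.

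**Step 4: scale and precision.** In the first three rows the standard deviation of the estimate is 0.241, 0.223 and 0.213, so the bias is 0.22 to 0.29 of a standard error. With the 3-month score it falls to 0.239, 0.218 and 0.205. In the last three rows it falls from 0.248, 0.231 and 0.213 to 0.245, 0.223 and 0.203. The gain in precision is about 1% to 5%.

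**The case against.** The strongest reply is that the covariate list need not be exhaustive. EM works on a joint distribution, the protocol plans repeated measures ANCOVA for these outcomes, and the 3- and 6-month scores may both have been variables in the EM run, with the list naming only what was added. That is possible, but no section says so. If it was done, the sentence needs correcting.

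The objections on scope stand. This is a sensitivity analysis, behind a complete-case primary strategy. The primary outcome has no 3-month scan. Women lost before month 3 have no early score to use. The bias is about a quarter of a standard error even in the one-arm case, and that case gives attendance no link to response; if poor responders also attended less, compliance would absorb some of it.

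Several stronger readings are tempting but not supported:

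- **The 3-month data are thrown away.** They may still enter the repeated measures analysis; what they do not inform is the filled 6-month value.
- **Dropouts are set to their arm's mean.** The prediction also uses baseline and attendance, and women who stopped training but were assessed help inform it.
- **One woman in five with a 3-month value is affected.** That holds only if nobody leaves before month 3.
- **The MRI imputation should borrow 3-month pain or strength.** Nothing in the protocol shows that either predicts cartilage change, and the Blinding section says follow-up performance testing was blinded for the participant only.

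**Conclusion.** The point holds within a narrow scope: secondary, non-MRI outcomes, in the intention-to-treat sensitivity analysis, for women lost after the 3-month visit. As written, the imputation ignores observed early response, and attendance is only a partial proxy for it.

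The illustrative bias is about 0.05 to 0.07 SD, favouring training, if poor-response dropout is confined to that arm. It is about 0.01 to 0.02 SD in the other direction if the mechanism is equal across arms. The loss of precision is small. These sizes rest on assumed correlations and an assumed dropout mechanism, since the protocol gives neither. A reader might infer that the primary cartilage result or the complete-case analysis is put in doubt by this omission; the protocol does not support that, because neither uses this imputation and cartilage has no 3-month measurement.

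**What to change.** In the Statistical analysis section, add each non-MRI outcome's own 3-month value to its EM imputation model, beside group, baseline score and compliance. Women without a 3-month visit keep the planned covariates, and the MRI outcomes keep the planned model. If the 3-month scores were already in the EM run, say so instead.

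The data are already collected, so the cost is analysis work and one sentence of text. Recruitment ended in December 2006 and results were expected in July 2009, so the change should be dated and reported as a change to the sensitivity analysis.
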